### Statistical analysis

2.6

Missing data will be addressed according the STROBE statement [47]. When data are missing <5% per variable per case, complete case analyses will be performed. The type of missing data will be first checked and reported. When necessary, multiple imputation will be performed before analysis.

To analyze cross-sectional differences between participants with and without LBP regarding the organization of M1 of trunk muscles and the performance on motor control and sensory tests, multivariate mixed model analyses will be used, with a 2-level structure. Regarding the organization of M1 of trunk muscles, the MEPs (i.e., longissimus at level L3 and L5, internal and external abdominal oblique muscles) are clustered within the participant. Regarding the motor control and sensory tests, the test scores are clustered within the participant. The same analyses will be used to analyze the association between the organization of M1 of trunk muscles and the performance on a motor control and sensory tests. For the latter, the organization of M1 of trunk muscles will be used as outcome.

To analyze changes over time in organization of M1 of trunk muscles and to analyze differences in changes over time between participants with LBP (recovered and non-recovered) and participants without LBP, multivariate mixed model analyses with a 3-level structure will be used. The MEPs are clustered within the repeated measurements and the repeated measurements are clustered within the participant. The same analytical procedure will be followed to analyze the differences in changes over time in performance on motor control and sensory tests between participants with LBP (recovered and non-recovered) and participants without LBP. In these multivariate mixed model analyses, time, group and the interaction between time and group will be added.

Finally, the longitudinal associations between organization of M1, and the motor control and sensory tests performance over time, will be analyzed with multivariate mixed model analyses. For the latter, again, the organization of M1 of trunk muscles will be used as outcome.

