### Participants

2.2

We included people with LBP (>24 h) [20] who were seeking medical or physiotherapy care, who either had chronic LBP (pain duration of >12 weeks) and had recently experienced a flare up, or people with recurrent LBP. LBP was defined as pain between the lower rib margins and the buttock creases [21]. A flare up was defined as an increase in pain of at least two points in pain intensity on a 0–10 Numeric Pain Rating Scale and also an increase in the impact of LBP on usual activity [22]. Recurrent LBP was defined as an episode of LBP lasting >24 h, separated by a pain-free period of more than one month without LBP [23], and where LBP had an impact on usual activity. With these selection criteria, we aimed to include people who were anticipated to experience fluctuations or recovery in pain and function. The following exclusion criteria were used: major spinal pathology, a history of lumbar radiculopathy or spinal operation, circulatory diseases, or pregnancy and the six-month postpartum period, younger than 18 or older than 65 years of age, or not meeting the safety criteria for Magnetic Resonance Imaging (MRI) or Transcranial Magnetic Stimulation (TMS) [24]. People without LBP had to be free of an episode of LBP in the preceding three years and were matched for sex and age to the people with LBP. People with LBP were recruited from five primary care physiotherapy clinics in The Netherlands. People without LBP were recruited from the acquaintances, friends, or relatives of the patients.

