#### Questionnaires

2.4.1

All participants completed a questionnaire regarding demographic variables. Participants with LBP also completed 1) a general questionnaire containing questions on location and duration of their pain; 2) a Numeric Pain Rating Scale (0–10); 3) the Oswestry Disability Index; 4) the Pain Anxiety Symptom Scale; and 5) the Central Sensitization Inventory. All questionnaires have adequate reliability and validity [[26], [27], [28], [29], [30]]. At 5-week follow-up, participants with LBP indicated their overall level of recovery on a Global Perceived Effect scale (GPE-Dutch Version, 7-point Likert scale) and completed the Numeric Pain Rating Scale, Oswestry Disability Index, Pain Anxiety Symptom Scale and Central Sensitization Inventory. Participants without LBP reported whether they were still free of LBP.

For our analyses, we are interested in those participants with LBP who showed recovery, versus those who did not. These groups (recovered and non-recovered LBP participants) are defined based on their ‘Global Perceived Effect’ after 5 weeks. The LBP participants is asked how much their back condition has improved or deteriorated on a 7-point Likert scale. Category 1 (‘completely recovered’) and category 2 (‘much improved’) will be considered as recovered. Category 3 (‘slightly improved’), 4 (‘equal’) and 5 (‘slightly deteriorated’) will be considered as ‘unchanged’, category 6 (‘much deteriorated’) and 7 (‘completely deteriorated’) as deteriorated. Therefore, category 3 till 7 will be considered as non-recovered [31].

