A Magstim 200^2^ stimulator (Magstim Company Ltd., Whitland, Dyfed, UK) was used to deliver a single-pulse TMS. The hemisphere contralateral to the side of the highest pain intensity was stimulated, using a figure-of-eight coil with 70 mm windings. The coil was orientated 45° to the sagittal plane, tangential to the scalp to induce currents in the cortex along the posterior to anterior direction [43]. Neural navigation software stored the position and orientation of the coil with respect to the head for each stimulation. The stimulation intensity was set at 100% output of the stimulator, as 120% of the motor threshold of the longissimus muscle generally exceeded the maximum output of the stimulator for most participants [9,10]. The hemispheres in the participants without LBP were measured corresponding to the hemispheres measured in the LBP participants.

During the TMS protocol, the EMG activity of the longissimus muscle at the level L3 of the painful site was monitored for the presence of MEPs. We used a protocol with 100 stimulations at pseudorandom positions using an interstimulus interval of approximately 4 s [42,44], covering the area of the motor cortex using a predefined 7 × 7cm grid, starting at the midline of the vertex. When we also found MEPs at the borders of the grid, stimulations were given in the surroundings, to make sure the area that can be stimulated was completely covered. The measurements were conducted according to the TMS checklist for methodological quality [45]. The MEPs of the other muscles were also recorded, but these were not monitored online. These data will also be reported and analyzed.

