### Sample size estimation

2.5

The sample size was calculated based on a cross-sectional comparison between two groups, using a continuous outcome, with a power of 0.80 and an α of 0.05. We used the mean and pooled standard deviation (0.68) regarding the CoG of the longissimus muscle from previous similar research, investigating the differences in CoG between the groups participants with LBP (n = 27; mean (SD): 1.4 (0.61)) and participants without LBP (n = 23; mean (SD:) 0.8 (0.77)) [9]. The calculation produced a required sample size of N = 21 per group. Taking a 15–20% drop out risk into account, the required sample size per group was 25.

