This study has some limitations. We defined the selection criteria in such a way that we anticipated a proportion of the participants to recover after five weeks. We therefore did not want to solely recruit people with persistent pain, but opted to include people with a fluctuating pain trajectory. However, it is possible that either the number of recovered or the number of non-recovered LBP participants will be small. This may influence the power of the statistical analysis. However, in general the power of longitudinal analyses is higher than the power of cross-sectional analyses, because of the gain in the number of observations. Despite some loss because of the partly correlated observations, more observations will remain for the analysis than in a cross-sectional design. Based on the sample size calculation, for the comparison between participants with LBP and participants without LBP of cortical reorganization over time, the power is therefore expected to be sufficient.

Although people with longer lasting symptoms might be more prone to reorganization of M1, we decided to include participants with a pain duration >24 h [20] who were seeking medical or physiotherapy care, since a marked improvement is expected in the first six weeks of a LBP episode [25].

In this study we used 100% of the maximum stimulator output, as 120% of the motor threshold of the longissimus muscle generally exceeds the maximum output of the stimulator [9,10]. Therefore, no individual stimulation intensity was used. Subsequently, for some participants the stimulation intensity could be too high for accurate determination of the area [43] and for others too low for inducing MEPs.

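### Controls are matched on sex and age, but the described models name neither factor: this costs precision cross-sectionally and leaves the association and recovery analyses unprotected

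*Protocol article*

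**What the plan says.** Under Participants, the controls "were matched for sex and age to the people with LBP". They were recruited among the patients' acquaintances, friends or relatives, and all participants are aged 18 to 65. Under Reorganization of M1: "The hemispheres in the participants without LBP were measured corresponding to the hemispheres measured in the LBP participants". Whether matching was one-to-one or by frequency is not stated.

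Under Statistical analysis, the cross-sectional group comparison is described thus: "multivariate mixed model analyses will be used, with a 2-level structure". The same approach serves the cross-sectional associations, with M1 organization as outcome. For the longitudinal group comparison: "The MEPs are clustered within the repeated measurements and the repeated measurements are clustered within the participant", and "time, group and the interaction between time and group will be added". The longitudinal associations again take M1 organization as outcome. The section mentions age, sex or a pair level for none of these.

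Under Questionnaires, the recovered and non-recovered groups "are defined based on their ‘Global Perceived Effect’ after 5 weeks". The Discussion concedes that "it is possible that either the number of recovered or the number of non-recovered LBP participants will be small" and treats this as a matter of power.

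**The concern.** Matching makes the two groups alike on age and sex. An analysis that ignores the matching factors leaves their variance in the error term, although the design has already removed it from the group difference. The standard error is then larger than the true sampling variation of that difference.

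Two further analyses get little or no help from the matching. An association between M1 organization and a test score is estimated across people of different ages and both sexes, and if age or sex affects both variables it creates or hides an association. The recovery groups are formed within the LBP group after matching, so they need not resemble each other or the controls on age and sex. At stake are efficiency in the cross-sectional contrast and confounding in the other two.

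**Working it through.** **Inputs.** Mean CoG 1.4 versus 0.8 (difference 0.6), pooled SD 0.68, calculated "with a power of 0.80 and an α of 0.05" (Sample size estimation); 25 per group (Abstract). The share of outcome variance explained by age and sex, R², is not given. I assume 0.1, 0.2 and 0.3.

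**The plan's own figure.** n per group = 2 × (1.96 + 0.842)² × (0.68/0.6)² = 2 × 7.85 × 1.284 = 20.2, rounded up to 21. The stated 21 reproduces as a two-sided comparison of two independent groups, with no credit taken for matching. The sample size is not at fault here.

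**Cross-sectional LBP versus no LBP, exact matching.** The estimate is the same with and without adjustment. The unadjusted standard error is too large by 1/√(1 − R²), and adjusting is worth 1/(1 − R²) in participants. The true size of a nominal 5% test is about P(|Z| > 1.96/√(1 − R²)): cut-offs 2.066, 2.191 and 2.343 give 0.039, 0.028 and 0.019. A simulation of 21 exactly matched pairs (10,000 runs per setting) agrees:

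| R² | CI too wide by | Worth in participants | Type I error, unadjusted / adjusted | Power, unadjusted / adjusted |
|---|---|---|---|---|
| 0 | 0% | 0% | 0.048 / 0.048 | 0.79 / 0.79 |
| 0.1 | 5% | 11% | 0.040 / 0.049 | 0.80 / 0.83 |
| 0.2 | 12% | 25% | 0.028 / 0.048 | 0.82 / 0.87 |
| 0.3 | 20% | 43% | 0.019 / 0.047 | 0.84 / 0.92 |

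**Time-by-group term.** With two visits and complete data, this term compares mean within-person changes. If the outcome is b × age plus other terms at both visits, b × age drops out of the change. A main effect of age or sex therefore alters neither the estimate nor its standard error, and the percentages above do not apply. Only an effect of age or sex on the change itself matters, and that needs a covariate-by-time term.

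**Association models.** Reduce the model to one correlation in 50 people with no true association. Suppose one common factor, such as age, explains R² of both variables in the same direction. The induced correlation is then √R² × √R² = R². By Fisher's z, with standard error 1/√47 = 0.146, the expected test statistics are 0.69, 1.39 and 2.12. The chance of a false positive at the 5% level is about 11%, 28% and 56%. A simulation gave 11%, 29% and 57%, against about 5% with adjustment. Effects in opposite directions would induce a negative correlation or mask a real positive one.

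**Recovery groups.** For a split a/b of the 25 LBP participants, the standardised age difference has standard error √(1/a + 1/b). The splits are assumed.

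| Split | SE | P(age difference above 0.5 SD) by chance |
|---|---|---|
| 12/13 | 0.40 | 0.21 |
| 8/17 | 0.43 | 0.24 |
| 5/20 | 0.50 | 0.32 |

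Any real link between age or sex and recovery adds to this.

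**The case against.** The strongest reply is that a journal article need not list covariates: the full protocol or analysis plan may do so, and nothing in the article rules out adjustment. That stands in part. The sentence on time, group and their interaction does not say that these are the only terms, and it covers the longitudinal group models alone. A reader might infer that adjustment is excluded everywhere; the text does not support that. The article does, however, set out the levels and the longitudinal terms, and that description leaves out a feature of the design that it reports itself.

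A reader might also infer that the matching is wasted. It is not. It still balances LBP against no LBP, the estimate is unbiased, and the unadjusted test errs on the safe side.

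A third tempting reading is that the interval widening applies to the longitudinal models, or that main-effect covariates would repair the recovery contrasts of change. Neither is so, because stable effects on level cancel in the time-by-group term.

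Finally, the hemisphere rule and the recruitment of friends and relatives suggest one-to-one pairing but do not state it. Nor does the article say that a control is an acquaintance of his or her own matched case. A pair effect cannot be the main remedy on that evidence. It would also add a level to an already demanding model with at most 50 people.

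**Conclusion.** The point holds in a limited form. As described, the models do not use the factors on which the controls were matched. For the cross-sectional group contrast the consequence is lost precision and a test below its nominal level (0.040 to 0.019 for R² of 0.1 to 0.3), without bias. For the associations between M1 organization and the motor control and sensory tests, which are a stated aim, the consequence can be confounding. For the recovery groups, age and sex balance is not secured by design; this matters for comparisons of level, and for comparisons of change only if age or sex affects the change.

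The sizes rest on assumed values of R², on exact matching, on complete data for the cancellation argument, and on a single-correlation simplification of the association models. The documents give no figure for how strongly age or sex relates to any outcome. If R² is near zero, little is lost and little gained. This is a worthwhile improvement, not a flaw that invalidates the main comparison.

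**What to change.** State, before the analysis, that:

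- Age (continuous) and sex enter as fixed covariates in the cross-sectional group models and in both the cross-sectional and the longitudinal association models.
- The longitudinal models comparing recovered, non-recovered and control participants include age and sex with their interactions with time, at least as a sensitivity analysis, since a recovery group may be small.
- A random intercept for the matched pair is fitted only as a sensitivity analysis for LBP versus no LBP, and only if matching was one-to-one. The article should say which kind of matching was used.

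The matching factors should already be on file, so no new data are needed. The cost is wording plus two degrees of freedom for the main effects, or four with the time interactions. Fixing the covariates now also prevents their being chosen after seeing the results across many outcomes.

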## Abstract

**Background:**

In people with low back pain (LBP), altered motor control has been related to reorganization of the primary motor cortex (M1). Sensory impairments in LBP have also been suggested to be associated with reorganization of M1. Little is known about reorganization of M1 over time in people with LBP, and whether it relates to changes in motor control and sensory impairments and recovery. This study aims to investigate 1) differences in organization of M1 of trunk muscles between people with and without LBP, and whether the organization of M1 relates to motor control and sensory impairments (cross-sectional component) and 2) reorganization of M1 over time and its relation with changes in motor control and sensory impairments and experienced recovery (longitudinal component).

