Little is known about changes of the CoG of trunk muscles over time in people with LBP, and how this relates to recovery. A proof-of-principle study revealed an anterior and medial shift of the CoG of the transversus abdominis muscle following exercises of contraction of this muscle, whereas in the control intervention of self-paced walking no changes were observed [7]. In addition, a prospective cohort study revealed that a smaller L3 map volume was a predictor for LBP at 6-months follow-up, in contrast to the CoG which revealed not to be a predictor [18].

Sensory impairments are also suggested to be associated with reorganization of M1 [3,19]. Adaptive motor behavior in people with LBP may lead to selective muscle activation and kinematics. This will lead to a change in sensory feedback from the lumbar area. This, in turn, might contribute to neuroplastic changes in the motor and sensor cortex and to proprioceptive impairments reducing the ability to control lumbar movement [3]. This suggested relation has hardly been studied, and has not yet been demonstrated [12].

Because of the scarce and inconsistent evidence, there is a need for a better understanding of the relations between motor control changes, sensory changes, and M1 reorganization of trunk muscles in people with LBP. To investigate this relation, we will conduct a case-control study with both a cross-sectional and longitudinal component. The aim of the cross-sectional part is to investigate differences between people with LBP and without LBP regarding the reorganization of M1 of trunk muscles, and the performance on motor control and sensory tests. In addition, the association between the organization of M1 and the performance on motor control and sensory tests will be studied. The aim of the longitudinal part is to analyze reorganization of M1 of trunk muscles as well as changes in motor control and sensory test performance over time, within and between people with LBP (recovered and non-recovered) and without LBP. In addition, the associations between reorganization of M1, and changes in motor control and sensory test performance over time, and between groups, will be studied.

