### Procedure

2.3

All participants were measured twice with an interval of five weeks (± one week), since a marked improvement is expected in the first six weeks of a LBP episode [25]. During this five-week interval, the participants with LBP received usual care in a primary care physiotherapy clinic. The therapists of these clinics received information about possible exercises for motor control and sensory accuracy, but were free in their choice of therapy form, duration, and intensity. However, during therapy they were not allowed to use the tests of which the results served as outcomes in the present study. All participants first underwent a T1 weighted MRI of the brain, after which they completed self-reported questionnaires, performed quantitative sensory tests, a motor control test, sensory tests and underwent TMS to determine the organization of M1. The MRI was only conducted before the first measurement. Below, each of these assessments is described in detail. See Fig. 1 for a flowchart of the study.

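### As written, the longitudinal association model does not separate within-person from between-person association, so its slope does not isolate whether change in M1 goes with change in the tests

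*Protocol article*

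**What the plan says.** The aims are worded in terms of change. The Introduction says that "the associations between reorganization of M1, and changes in motor control and sensory test performance over time, and between groups, will be studied". The abstract describes the longitudinal component as "reorganization of M1 over time and its relation with changes in motor control and sensory impairments and experienced recovery (longitudinal component", and the Discussion repeats this. The association between levels at one time point is a separate, cross-sectional aim with its own analysis.

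The analysis is worded in terms of level. Section 2.6 (Statistical analysis) states that "the longitudinal associations between organization of M1, and the motor control and sensory tests performance over time, will be analyzed" with multivariate mixed models, and adds: "For the latter, again, the organization of M1 of trunk muscles will be used as outcome". Just before this, the models for change over time by group are specified: "In these multivariate mixed model analyses, time, group and the interaction between time and group will be added". That sentence belongs to the group-comparison models. For the association model the article names no change score, person mean, deviation term or test-by-group term.

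There are two time points (section 2.3, Procedure): "All participants were measured twice with an interval of five weeks (± one week".

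**The concern.** A mixed model with a level as outcome and the concurrent level of a test as predictor draws on two comparisons. One is between people: do those with worse scores have different maps? The cross-sectional analysis already asks that. The other is within people: when a person's score changes over five weeks, does the map change too? A random intercept deals with the dependence between a person's two visits, but it does not keep the two comparisons apart. A single slope is a precision-weighted average of both.

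What is at stake is the interpretation of one of the longitudinal results. A longitudinal association could be reported although the changes are unrelated, because a stable cross-sectional relation feeds the coefficient. Equally, a true link between the changes could be diluted.

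**Working it through.** **The plan's own figure.** The article gives no figure for this model. Its only calculation is the cross-sectional sample size in section 2.5, "with a power of 0.80 and an α of 0.05", with means 1.4 and 0.8 and SD 0.68:

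n = 2 × (1.960 + 0.842)² × (0.68 / 0.60)² = 2 × 7.85 × 1.284 = 20.2, so 21 per group.

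This reproduces the stated 21 (two-sided alpha; power at 21 by the t-test is 0.797). It concerns a different comparison and says nothing about the association model. What is taken from section 2.5 is the planned 25 per group, that is N = 50.

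**Inputs that must be assumed.** The article gives no visit-to-visit correlation for the test (rx) or the map (ry), and no between-person correlation. All three are assumptions below and are varied.

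**Step 1: what the single slope estimates.** Take a random-intercept model with two visits per person and standardized variables. The information on the slope is proportional to:

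- within person: (1 − rx) / (1 − ry)
- between persons: (1 + rx) / (1 + ry)

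The within-person weight is the first divided by the sum of both.

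| rx (test) | ry (map) | within term | between term | within-person weight |
|---|---|---|---|---|
| 0.7 | 0.7 | 1.00 | 1.00 | 50% |
| 0.7 | 0.5 | 0.60 | 1.13 | 35% |
| 0.9 | 0.5 | 0.20 | 1.27 | 14% |
| 0.5 | 0.9 | 5.00 | 0.79 | 86% |

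The weight is 50% whenever rx = ry and runs from 14% to 86% over 0.5 to 0.9. The less a test changes between visits relative to the map, the more the slope is a cross-sectional one.

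**Step 2: consequence when the changes are unrelated.** The simulation had 50 participants, two visits, a true within-person slope of 0, one outcome and one predictor. Stable parts of test and map were correlated at 0.3 or 0.5, and the map's visit-to-visit correlation was 0.6. The unsplit model had the test score and time. The split model had deviation, person mean and time. There were 400 runs per setting.

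| rx | between-person correlation | mean unsplit slope | unsplit slope significant | within-person slope significant |
|---|---|---|---|---|
| 0.5 | 0.3 | 0.10 | 19% | 6% |
| 0.5 | 0.5 | 0.18 | 43% | 5% |
| 0.7 | 0.3 | 0.13 | 28% | 5% |
| 0.7 | 0.5 | 0.23 | 58% | 6% |
| 0.9 | 0.3 | 0.21 | 42% | 6% |
| 0.9 | 0.5 | 0.33 | 83% | 7% |

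A second simulation used 1,500 trials per setting and the pairs (rx, ry) = (0.5, 0.5), (0.7, 0.7), (0.8, 0.5) and (0.8, 0.8). The unsplit slope was significant in 17% to 30% of trials at a between-person correlation of 0.3, and in 42% to 69% at 0.5. Change regressed on change rejected in about 5%. This is the source of the summary range of roughly 17% to 70%; the 83% above arises only with a very stable test.

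**Step 3: would the terms already named help?** Adding time, group and time × group to the unsplit model left the rates at 19% to 31% (correlation 0.3) and 45% to 71% (correlation 0.5). Carrying over the terms of the preceding models therefore does not solve the problem.

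**The case against.** The strongest objection is that the defective model is inferred. Section 2.6 does not say how the test scores enter. The proposed remedy is itself a mixed model with M1 organization as outcome, so the text does not exclude it, and an article may leave coding of predictors to a fuller plan. This stands as a limit: the point can only be made about the plan as written, and confidence is moderate. It does not remove the point. The article fixes a level as outcome for an aim about change, and the plain reading gives the mixed slope.

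Four further objections stand in part.

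- A reader might infer that the planned model cannot answer the aim at all. The article does not support that. The slope carries within-person information, up to 86% of the weight in the range shown, and it is the change-change slope if both slopes agree. It fails to isolate associated change.
- A reader might infer that the whole longitudinal conclusion falls. It does not. The Introduction first asks for change within and between the recovered, non-recovered and pain-free groups. That question has its own three-level model, which this point leaves untouched.
- The rejection rates rest on assumed correlations and on a simpler model than the planned multivariate one. They also detect a between-person association that is real in the simulation, so the harm is calling it change, not inventing a signal.
- The split model equals change regressed on change only for complete pairs with a time term, and section 2.5 expects 15–20% dropout.

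**Conclusion.** The concern holds for the plan as written. The aim is about changes going together; the model, read plainly, relates levels over two visits and does not separate the two sources of association. Its slope answers the aim only if the within-person and between-person slopes are equal, and the article neither states nor tests this.

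The size cannot be fixed from the document. It depends on the assumed visit-to-visit and between-person correlations, and the rates quoted are conditional on those. In every setting tested with a non-zero between-person correlation, the unsplit slope was significant well above the nominal 5% when the changes were unrelated.

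This should be fixed, but it does not threaten the study. Data collection, the sample size and the models for change by group are unaffected.

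**What to change.** In the longitudinal association model, replace each test score by two terms: the person's mean over the two visits, and the deviation of each visit from that mean. Include time and group. Base any statement that change goes with change on the deviation coefficient alone, and report the coefficient of the person mean separately as the between-person association. For participants with both visits, and with time in the model, the deviation coefficient equals that from regressing change in M1 on change in the test.

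The Introduction also asks about differences between groups. A group × deviation term would address this, but it should be labelled exploratory, because the Discussion itself warns that the recovered or the non-recovered group may be small.

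The cost is a few sentences in the plan and two derived columns per test, with no new data and no change in sample size, provided it is settled before the analysis. The confidence interval of the within-person coefficient will be wider than that of the mixed slope, and participants with only one visit add nothing to it.
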